### Sample size calculation

The sample size calculation will be based upon a retrospective analysis of the change in eGFR in patients with stage 4 CKD treated at our hospital between 2003 to 2010, and Hou’s trial published in 2006 [12]. Our retrospective analysis indicated that the mean eGFR decrease was 4.5 ± 4.2 ml/min/1.73 m^2^ per year in patients with stage 4 CKD treated with CM. Hou’s trial reported that the median rate of GFR decrease was around 6.8 ml/min/1.73 m^2^ per year in patients with stage 4 CKD receiving benazepril [12]. PASS 2008 software (NCSS, LLC, Kaysville, Utah, USA) was used to calculate the sample size required for the current study to allow a superiority test to be performed for the BYF group versus the losartan group where 1 ml/min/1.73 m^2^ GFR is considered to indicate a clinically important difference with a 90 % power and a one-tailed significance level of 2.5 %. The study was calculated to require 221 patients per group. Predicting a 20 % lost to follow-up rate, we adjusted the total sample size to 277 for each group.

### Statistical analyses

An independent team of data managers and statisticians from KUMCR, will be responsible for the data management and statistical analysis of this study. The statisticians will be blinded to the randomized allocation of groups. PAWS 18.0 (IBM SPSS Inc., Armonk, New York, USA) and SAS 9.2 (SAS Institute Inc., Cary, USA) statistical software packages will be used to analyze the data.

Prior to analyses, the statistical analysis plan will be written, updated and confirmed after blind data review. The full analysis population is defined as patients randomized to receive at least one treatment dose, with baseline and at least one post-baseline efficacy assessment. The per-protocol population is defined as patients who complete the course of the study without a major protocol violation. The primary outcome analysis is based on full analysis population, intention-to-treat principle and the per protocol population. An intention-to-treat analysis will be applied using the imputation method for missing data. The linear trend at point method will be used to replace missing values. The existing series will be regressed on an index variable scaled 1 to n, and the missing values will be replaced with their predicted values. If the predicted values cannot be computed, the last observation carried forward (LOCF) method will be used for this variable. For analysis of endpoint events, a mixed effect model will also be employed, adjusting for co-variables including baseline characteristics. After reporting descriptive statistics of baseline characteristics for each group, an effectiveness analysis will compare the BYF and losartan groups, and a superiority test, with a 95 % confidence interval for eGFR, will be performed to investigate the clinical difference associated with BYF.

The eGFR will be analyzed using a mixed effect GLM with terms for treatment, time point, center, and some baseline characteristics as co-variables based on the concept of repeated measure analysis or adjusted nominal significance level. The Mann–Whitney U-test will be used to analyze ordinal categorical variables. An analysis of variance (ANOVA) will be used for numerical variables, and a Chi-square test or Fisher exact test will be used for categorical variables.

An analysis of covariance will be used for continuous variables, and the Cochran–Mantel–Haenszel test will be used for categorical variables to adjust for the center effect. Unconditional logistic regression analysis will be used for the curative effect factors analysis. The Kaplan–Meier method will be used to assess the incidence and mean occurrence time of endpoint events. Cox proportional hazards regression will be used to analyze factors influencing the incidence of endpoint events. Subgroup analysis of risk factors including hypertension, proteinuria will be performed. The Fisher exact test will be used to compare the incidence rates of AEs and adverse drug reactions over the course of treatment.

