### Outcome measurements

#### Primary outcome

The primary outcome is the change in eGFR over 12 months. Decline of eGFR has been widely applied as primary outcome in several trials, such as the Hypertension (AASK) [20], MDRD Study [21] and the Ramipril in Non-diabetic Renal Failure Study (REIN) [22]. The eGFR will be calculated by the CKD-EPI (Chronic Kidney Disease Epidemiology Collaboration) formula [23], and evaluated at baseline, and after 3, 6, 9 and 12 months of the follow-up period.

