### Termination and withdrawal

Patients failing to complete the clinical observation will be classified as case dropouts. Investigators will contact these patients and attempt to record the reason for dropping out and the last time they took the studied medicine. Participants will be withdrawal from the study in any of the following situations: 1) commencing permanent renal replacement therapy (dialysis >30 days or kidney transplantation); 2) severe infection, hyperkalemia (K^+^ > 6.5 mmol/L), acidosis (TCO_2_ < 13 mmol/L), or heart failure not curable by medication, deterioration of kidney function that demands dialysis, massive hemorrhage of the gastrointestinal tract, serious arrhythmia dependent on anti-arrhythmic drugs, or uremic encephalopathy; 3) severe primary disease such as an active-stage malignant tumor, decompensating liver cirrhosis, or hematopoietic system disease; 4) urinary tract obstruction that requires surgical treatment; 5) death; 6) withdrawal of consent; 7) transfer to a renal unit which is not an active study site.

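### The per-protocol set is limited to completers, so its membership depends on renal outcome, yet it stands unranked beside the full analysis set as a basis of the primary analysis

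*Protocol article*

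**What the plan says.** All sections are in the protocol article.

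- **Statistical analyses, definition.** "The per-protocol population is defined as patients who complete the course of the study without a major protocol violation". Completion is a condition of its own, in addition to the absence of a major violation.
- **Statistical analyses, role.** "The primary outcome analysis is based on full analysis population, intention-to-treat principle and the per protocol population". The sets are listed together. None is called decisive or supportive.
- **Statistical analyses, full analysis population.** It needs one dose, a baseline value and at least one post-baseline efficacy assessment. Completion is not required.
- **Termination and withdrawal, status.** "Patients failing to complete the clinical observation will be classified as case dropouts".
- **Termination and withdrawal, reasons for leaving the study.** These include "commencing permanent renal replacement therapy (dialysis >30 days or kidney transplantation"), "deterioration of kidney function that demands dialysis" and, further down the list, "5) death; 6) withdrawal of consent". A potassium limit is also listed, as "hyperkalemia (K^+^ > 6.5 mmol/L"), in a run of conditions where a later phrase about failure of medication may or may not qualify it.
- **Primary outcome.** "The primary outcome is the change in eGFR over 12 months".
- **Secondary outcomes.** Permanent dialysis, transplantation and death are endpoint events.

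**The concern.** A per-protocol set is meant to select on eligibility and adherence. Here it also selects on reaching the end of the study, and several listed reasons for not reaching it are the end stage of the process that the primary outcome measures. A patient who takes every dose and starts permanent dialysis in month 8 has followed the protocol but is not in the set. Those removed are, on average, the fastest decliners, so the set compares slower progressors who survived. If the arms lose such patients at different rates, the randomised comparison is distorted.

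This would matter little in an analysis labelled supportive. It matters here because the set is one of the stated bases of the primary analysis. If the full analysis and per-protocol results disagree, the protocol does not say which carries the superiority claim.

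**Working it through.** **1. The passages side by side.** Per-protocol requires completion. Termination and withdrawal takes patients out of the study, not only off treatment, at permanent renal replacement therapy, dialysis-demanding deterioration and death, and classes non-completers as dropouts. Such patients have not completed, so they are outside the set whatever their adherence.

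**2. The plan's own figure.** From Sample size calculation: declines 4.5 (SD 4.2) and 6.8, clinically important difference 1, power 90 %, one-sided 2.5 %. Treating 1 as a superiority margin, the effect beyond it is (6.8 − 4.5) − 1 = 1.3.

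n = 2 × 4.2² × (1.960 + 1.282)² / 1.3² ≈ 219.3, so 220 per group. The noncentral t version gives 221, as stated, and 221 / 0.8 = 276.25 rounds up to 277, also as stated. The sample size is not in dispute.

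**3. Illustration of the selection.** The protocol gives neither event rates nor an eGFR at which dialysis starts. Assumptions:
- baseline eGFR uniform on 15–30 (the stage 4 range);
- linear decline, annual change normal with means −4.5 (BYF) and −6.8 (losartan), SD 4.2;
- a patient leaves if eGFR at month 3, 6 or 9 is below an assumed cutoff.

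Month 12 is not used as an exit visit, because a patient measured then has completed and supplied the endpoint. By simulation:

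| Cutoff | BYF removed | Losartan removed | Mean decline of those left, BYF | Losartan | Difference | Shift from 2.3 |
|---|---|---|---|---|---|---|
| 8 | 1.3 % | 3.5 % | 4.39 | 6.55 | 2.16 | 0.14 |
| 10 | 4.1 % | 8.7 % | 4.22 | 6.31 | 2.09 | 0.21 |
| 12 | 9.7 % | 17.2 % | 3.96 | 6.00 | 2.04 | 0.26 |

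The planned standard error of the difference is 4.2 × √(2/221) ≈ 0.40, so these shifts are about 0.35 to 0.65 standard errors. The distance above the margin of 1 falls from 1.30 to between 1.16 and 1.04.

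**4. The same model with other true effects.** With equal declines in both arms, removal is equal and the difference among those left is 0.00. With a true difference of exactly 1 (declines 4.5 and 5.5), it is 0.95, 0.92 and 0.89. Selection pulls towards no difference.

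**5. Unequal removal imposed by assumption.** If the worst fraction q of an arm is removed, its mean improves by SD × φ(z_q)/(1 − q). With SD 4.2 this is 0.46 for 5 %, 0.82 for 10 % and 1.15 for 15 %. With no true difference, removing 5 % of one arm and 10 % of the other gives a spurious 0.36; 5 % against 15 % gives 0.70. The arm that loses more patients looks better. This shows what differential removal could do, not what the protocol predicts.

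**The case against.** **The ranking of sets belongs in the statistical analysis plan, and completion is a common per-protocol condition.** This stands in part. The article says such a plan will be written and confirmed after blind data review, and a supportive per-protocol analysis would be ordinary in a superiority trial. But the article does not leave the matter open: it fixes completion as a condition and lists the set as a basis of the primary analysis.

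**The full analysis population protects the trial.** This stands. A reader might infer that the primary result rests on survivors alone. It does not: most early failures remain in the full analysis set, intention-to-treat has its own imputation rule, and endpoint events have Kaplan–Meier and Cox analyses.

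**The type I error rate is not shown to be inflated.** This stands. Inflation would follow if success in any one set were enough, but the article states no such rule. If success were required in every set, the error rate would not exceed that of a single test.

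**Nothing shows a false claim for BYF.** This stands for the model in steps 3 and 4. A spurious advantage needs removal that differs by arm for reasons other than decline. The Background links hyperkalaemia and acute kidney injury to the losartan drug class, so differing removal is plausible, but neither its size nor its net direction can be derived from the documents.

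**Completion is not defined.** The Discussion speaks of following patients until they reach an endpoint, so reaching one might count as completing. That passage, however, describes patients still free of endpoints when the trial ends. Termination and withdrawal is the more direct text, and it treats the others as withdrawn.

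**Hyperkalaemia.** A reader might infer that every patient above 6.5 mmol/L is removed. The list can also be read as covering only cases that medication does not resolve, so this item is uncertain. The renal replacement and death items do not depend on it.

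**Conclusion.** The point holds in a limited form. As written, one stated basis of the primary analysis is a set whose membership depends on the outcome, and no text says that another set decides. Under the planned declines and the assumptions of step 3, a true difference of 2.3 appears as about 2.2, 2.1 or 2.0: a shift of roughly 0.14 to 0.26 against a clinically important difference of 1, towards no difference and nil when the arms decline equally. Those figures rest on an assumed baseline distribution, linear decline, the assumed exit cutoffs and the use of a median benazepril decline as the losartan mean. The documents support neither a manufactured benefit for BYF nor a lost error rate. What they support is an ambiguous primary conclusion and a poorly defined set, both cheap to repair.

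**What to change.** In Statistical analyses:

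1. Name the full analysis/intention-to-treat analysis as the single decisive analysis for the superiority claim, and the per-protocol analysis as supportive only. This is the essential change.
2. Preferably, define per-protocol by eligibility, adherence and absence of major violations up to month 12, or up to the first endpoint event or protocol-mandated withdrawal if earlier, so that these patients are not excluded merely for not completing.
3. Clarify whether the phrase about failure of medication applies to the potassium item, so that membership can be determined. This asks only for the text to be made unambiguous; the withdrawal criteria themselves are not questioned.

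The cost is a wording change before unblinding, with no added patients or procedures and no change to 221 or 277 per group. A small downside of item 2 is that the per-protocol set then contains truncated follow-up. The planned mixed model can use it, though its interpretation needs a sentence.

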#### Secondary outcomes

The secondary outcomes include urinary protein creatinine ratio, serum creatinine level, biochemical test, cardiovascular function, quality of life and endpoint events (Table 1).

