**Table 1 Tab1:**
[figure not shown]
Schedule of study

The urinary protein creatinine ratio will be examined at baseline, and at 3, 6, 9 and 12 months. Serum creatinine level (SCr) and blood urea nitrogen level (BUN) will be measured at baseline, and at 1, 2, 3, 6, 9, and 12 months. Biochemical tests including plasma albumin, triglyceride, cholesterol, calcium, phosphate, and intact parathyroid hormone level (iPTH) will be measured at baseline, and at 3, 6, 9, and 12 months.

We will assess the patient's cardiovascular function by left ventricular ejection fraction (LVEF), interventricular septal thickness (IVST), left ventricular posterior wall thickness (LVPWT), carotid artery intima-media thickness (CIMT) through the Carotid Doppler and Cardiac Doppler, which will be measured at baseline and 12 months.

The Kidney Disease Quality of Life Instrument (KDQOLSF 1.3) scale will be evaluated at baseline and at 6 and 12 months.

Endpoint events are defined as serum creatinine level increasing to double the baseline level, ESRD (requiring permanent dialysis or kidney transplantation), cardiovascular or cerebrovascular events (acute myocardial infarction, heart failure, ischemic cerebral infarction or cerebral hemorrhage verified by typical clinical manifestations, electrocardiogram (ECG) alterations, and imaging and laboratory investigations) or death. The nature and severity of events will be recorded as endpoint events during the follow-up period.

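### Filling missing values by regression on visit order does not suit serum creatinine and BUN, whose visits are unequally spaced; a minor point that leaves eGFR on its own schedule unaffected

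*Protocol article*

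**What the plan says.** The imputation rule is in the protocol article under Statistical analyses. It opens with "The linear trend at point method will be used to replace missing values" and then defines the method: "The existing series will be regressed on an index variable scaled 1 to n, and the missing values will be replaced with their predicted values". The fallback is also stated: "If the predicted values cannot be computed, the last observation carried forward (LOCF) method will be used for this variable". The rule neither names nor exempts any variable, and nothing tells the analyst to use calendar time.

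Two visit schedules matter. Under Primary outcome, eGFR is "evaluated at baseline, and after 3, 6, 9 and 12 months of the follow-up period". Under Secondary outcomes, in the text after Table 1: "Serum creatinine level (SCr) and blood urea nitrogen level (BUN) will be measured at baseline, and at 1, 2, 3, 6, 9, and 12 months". SCr is named in the list of secondary outcomes. BUN is not in that list, but it is described with SCr in the same section.

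Under Sample size calculation, the expected loss is given: "Predicting a 20 % lost to follow-up rate, we adjusted the total sample size to 277 for each group".

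**The concern.** A line fitted to visit order is a line in time only if the visits are equally spaced. For SCr and BUN the steps are 1, 1, 1, 3, 3 and 3 months. The index gives all six the same length, so a patient whose creatinine lies exactly on a straight line in time is not given values on that line.

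For a patient who leaves early, the dense early visits make the slope per index step too shallow for the later quarterly steps. The filled month-12 change is then too small. Early leavers look more stable than their own trend, the arm means move towards no change, and if one arm loses more patients it looks better than it should. The protocol assigns analysis of variance and covariance to numerical and continuous variables, so a month-12 comparison of SCr or BUN could rest on such filled values.

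**Working it through.** **Inputs.** Index rule (Statistical analyses); SCr and BUN at months 0, 1, 2, 3, 6, 9, 12, that is, index 1 to 7 (Secondary outcomes); eGFR at months 0, 3, 6, 9, 12 (Primary outcome); 20% loss (Sample size calculation). The 20% is a share of those randomised: 221 / 0.80 = 276.25, rounded up to the stated 277. The protocol gives no figure for imputation error, so there is none to reproduce.

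**Set-up.** Take a noiseless patient whose value equals the month number, so the true month-12 change is 12. Fit least squares to the observed visits on the index and predict at index 7: fill = mean value + slope × (7 − mean index).

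**Single filled value, all earlier visits observed.**
- Last seen month 3: index 1-4, values 0, 1, 2, 3. Slope 1; fill = 1.5 + 1 × 4.5 = 6.0, which is 50% of 12. Last seen month 1 or 2 gives the same 6.0.
- Last seen month 6: index 1-5, values 0, 1, 2, 3, 6. Slope = 14/10 = 1.4; fill = 2.4 + 1.4 × 4 = 8.0, or 67%.
- Last seen month 9: index 1-6, values 0, 1, 2, 3, 6, 9. Slope = 30.5/17.5 = 1.743; fill = 3.5 + 1.743 × 3.5 = 9.6, or 80%.

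Regression on actual months returns 12.0 in each case.

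**Other patterns.**
- Only months 0 and 9 observed: slope = 9/5 = 1.8; fill = 9 + 1.8 = 10.8, or 90%. This is the smallest shortfall over all patterns that include baseline and have month 12 missing.
- Month 3 alone missing: the mean index of the other six visits is 4 and their mean value is 30/6 = 5, so the fill at index 4 is 5.0 instead of 3.

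**eGFR.** On months 0, 3, 6, 9, 12 the index is 1 + month/3, an exact linear function of time. The same rule returns 12.0 at month 12 for every dropout time, so there is no error.

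**Arm level, equal loss.** Assume leavers share their arm's mean rise and that all 20% are last seen at the same visit. With r the ratio above, the mean change is multiplied by 1 − 0.20 × (1 − r):
- r = 0.50: 0.90
- r = 0.67: 0.93
- r = 0.80: 0.96

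With the same pattern in both arms, the difference between arms shrinks by the same 4-10%.

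**Arm level, unequal loss (assumed 25% versus 15%; the protocol gives no split).** With equal true mean rises, the spurious difference as a share of the mean rise is (0.25 − 0.15) × (1 − r) = 0.05, 0.033 and 0.02 for r = 0.50, 0.67 and 0.80, that is, about 2-5%.

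**Precision of the alternative axis.** With independent errors of SD σ at each visit, the standard error of the fitted line at month 12 for a patient seen at months 0-3 is:
- on months: σ√(1/4 + (12 − 1.5)²/5) = 4.7σ
- on the index: σ√(1/4 + (7 − 2.5)²/5) = 2.1σ

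**The case against.** **Scope and reading.** The imputation sentences follow directly on the sentence about the primary outcome analysis, and for eGFR the rule does no harm. The text does not say outright that the index is visit order within a patient, and the statistical analysis plan is still to be written. These points carry some weight. But the wording is general, the fallback speaks of the variable at hand, and visit order is the natural reading. The regressor is stated, and it is the wrong one for these two series; this is not a detail left open.

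**Size.** The 20-50% shortfall belongs to one filled value on a noiseless line. A reader might take it as the bias in the trial's results, which the documents do not support: at the planned loss the arm-level effect is 4-10%, and 10% needs every loss to be last seen by month 3. With equal loss the shrinkage works against a superiority claim. Some leavers will have started dialysis or died, and for them a month-12 creatinine on their own trend is not well defined. All of this stands.

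**Remedy.** Regression on months is unbiased for a straight line but much noisier when months 0-3 are extrapolated to month 12 (4.7σ against 2.1σ). That stands, and it is why changing the axis is not the preferred fix.

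**Reach.** A reader might infer that the primary outcome is distorted because eGFR is calculated from SCr. That would require SCr to be filled on its seven-visit series before eGFR is computed. The protocol does not say so, and it gives eGFR its own equally spaced schedule. Nor does it say that filled values count towards creatinine doubling as an endpoint event.

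**Conclusion.** The stated rule is wrong for SCr and BUN. A month-12 change filled for a patient on an exactly linear course is 50%, 67% or 80% of the true change when the last visit is month 3, 6 or 9 and nothing earlier is missing, and up to 90% with early gaps. At 20% loss in both arms, the mean change and the difference between arms shrink by about 4-10%. At an assumed 25% versus 15%, the arm with more loss gains about 2-5% of the mean rise.

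These figures assume that the index means visit order, that the rule is applied to SCr and BUN, that the course is linear, and that leavers follow their arm's mean rise. The primary outcome is unaffected provided eGFR is filled on its own schedule. Because only secondary laboratory outcomes are concerned, the priority is minor.

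**What to change.** - Analyse SCr and BUN with a mixed model on the observed values, using actual visit times, and do not fill them. The protocol already plans a mixed model for eGFR, so this extends an intended method.
- If single imputation is kept as a sensitivity analysis, regress these two series on months since randomisation (0, 1, 2, 3, 6, 9, 12) instead of the index.
- State that eGFR is not derived from index-filled SCr.

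The cost is a few lines in the statistical analysis plan and its code, with no new data. There are two drawbacks: a built-in routine that assumes equal spacing can no longer be used for SCr and BUN, and regression on months gives imprecise month-12 values for patients last seen by month 3, so it should not carry the main analysis.

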## Design and Methods

### Study design

This multi-center, double blind, double dummy, randomized controlled trial (RCT) will be conducted in China (see Fig. 1). Approximately 554 patients will be divided into the CM group or losartan group at a 1:1 ratio.

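### Missing eGFR is filled by an ambiguously worded single imputation that the planned mixed model does not need and that, depending on the reading, biases the treatment difference or inflates its variance

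*Protocol article*

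**What the plan says.** All references are to the protocol article.

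- **Imputation rule (Statistical analyses).** The intention-to-treat analysis uses a linear-trend replacement: "The existing series will be regressed on an index variable scaled 1 to n, and the missing values will be replaced with their predicted values". Where no such value is obtainable, "the last observation carried forward (LOCF) method will be used for this variable". No outcome is exempted, so the rule reaches the primary eGFR analysis.
- **Model (same section).** eGFR is to be analysed by a mixed-effect model on the repeated-measures principle, with treatment, time point, centre and baseline covariates.
- **Population (same section).** The full analysis population requires a baseline value and at least one later efficacy value. The intention-to-treat principle is named beside it, without a separate definition.
- **Visits (Primary outcome).** eGFR is evaluated at baseline and at 3, 6, 9 and 12 months.
- **Expected loss (Sample size calculation).** "Predicting a 20 % lost to follow-up rate".
- **Reasons for loss (Termination and withdrawal).** These include permanent renal replacement, deterioration that demands dialysis, and death.

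**The concern.** The rule creates one predicted value per gap, which the analysis then treats as a measurement. It adds no information to a likelihood-based mixed model, which already uses a dropout's observed visits under missing at random.

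The rule also has two readings:

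- **Across patients.** The series is the column of month-12 values and the index is the case number. Row order says nothing about eGFR, so each gap receives roughly the pooled mean of both arms. That pulls the arms together.
- **Within patient.** The series is one patient's visits and the index is the visit number. A line through two to four noisy points is extrapolated by 3 to 9 months, so the filled values are far noisier than real ones.

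The stakes are the primary estimate, the coverage of its interval, and the power that the sample size was meant to buy. The sample size leaves only 1.3 ml/min/1.73 m² between the expected difference and the margin.

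**Working it through.** **1. Inputs from Sample size calculation and Study design.** Decline with Chinese medicine: "the mean eGFR decrease was 4.5 ± 4.2 ml/min/1.73 m^2^ per year". Control decline: "the median rate of GFR decrease was around 6.8 ml/min/1.73 m^2^ per year". Expected difference: 6.8 − 4.5 = 2.3. Margin: "1 ml/min/1.73 m^2^ GFR is considered to indicate a clinically important difference". Test: "with a 90 % power and a one-tailed significance level of 2.5" per cent. Allocation 1:1; 221 evaluable and 277 randomised per arm.

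**2. The plan's own figure.** n = 2 × (1.960 + 1.282)² × 4.2² / (2.3 − 1)² = 219.4, so 220 by the normal formula and 221 with the noncentral t. Then 221 / 0.80 = 276.25, so 277. A difference of 1 tested against zero would need 371–372 per arm, and 2.3 against zero 71–72. The stated size is therefore a test of 2.3 against a margin of 1. With all 277 per arm complete, SE = 4.2 × √(2/277) = 0.357, and power = Φ(1.3/0.357 − 1.96) = 95%.

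**3. Across-patient reading, 20% loss at random.** Expected difference = 0.80 × 2.3 = 1.84, which leaves 0.84 above the margin. Power = Φ(0.84/0.357 − 1.96) = 65%. The bias is 0.46, so coverage = Φ(1.96 − 0.46/0.357) = 75%. Simulated trials give 58–66% power. If patients with low or fast-falling eGFR drop out more, the estimate is about 1.5–1.6, coverage about 40–53% and power about 30–41%, depending on the dropout model.

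**4. Within-patient reading.** Assumptions: linear decline, independent visit noise with SD σ, and variance of the true 12-month change held at 4.2² = 17.64. The noise variance of an observed change is 2σ². Regressing visits 1 to k on their index and predicting visit 5 gives these noise variances for the imputed change:

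| Last visit | Weights on observed visits in the imputed change | Noise variance |
|---|---|---|
| month 3 (k = 2) | −4, 4 | 32σ² |
| month 6 (k = 3) | −2.17, 0.33, 1.83 | 8.17σ² |
| month 9 (k = 4) | −1.5, 0, 0.5, 1 | 3.5σ² |

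Here 17.64 is the variance of the measured change, so the part due to true slopes is 17.64 − 2σ². With 20% dropout spread evenly over the three visits, the average factor is (32 + 8.17 + 3.5)/3 = 14.56. The total variance is 17.64 − 2σ² + 0.8 × 2σ² + 0.2 × 14.56σ² = 17.64 + 2.51σ². By the same step it is 17.64 + 6.0σ² if all dropouts leave after month 3, and 17.64 + 0.3σ² if only month 12 is missing. A completers-only analysis corresponds to 17.64/0.8 = 22.05, which is SE 0.399 and 90% power.

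| Assumed σ | SE, spread | Power, spread | Power, all after month 3 | Power, only month 12 missing |
|---|---|---|---|---|
| 1.0 | 0.381 | 93% | 88% | 95% |
| 1.5 | 0.410 | 89% | 78% | 95% |
| 2.0 | 0.447 | 83% | 66% | 94% |
| 2.5 | 0.491 | 75% | 54% | 93% |

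Simulation (277 per arm, 600 runs per scenario, every patient with a post-baseline value) agrees: 73–92% with dropout spread over visits, 54–88% with early dropout, 92–95% with only month 12 missing, and 81–94% with eGFR-dependent dropout. Mean estimates are 2.27–2.39, so there is little bias. At σ of 2 or more with random dropout spread over visits, the rule does worse than discarding the dropouts (simulated 82% against 89% at σ = 2, and 73% against 90% at σ = 2.5).

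**5. Mixed model on observed visits, no imputation.** Mean estimate 2.27–2.33 and power 91–95% in every scenario.

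**6. Against zero instead of the margin.** Simulated power stays at or above 94% throughout.

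**The case against.** The best defence is that an outcome measured at five scheduled visits is most naturally read as a within-patient series. On that reading the estimate is essentially unbiased in the full analysis population and its interval keeps about 95% coverage. The analysis plan is also to be settled at blind data review, and a per-protocol analysis stands beside the imputed one. The power figures rest on an assumed visit noise; at σ = 1, or if only month 12 is missing, the rule costs almost nothing. Missing at random is itself doubtful when patients leave for dialysis or death.

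Much of that stands, and it rules out three stronger conclusions that a reader might draw:

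- **That the rule costs most of the planned power.** Losing more than half of 90% happens only on the across-patient reading combined with progression-related loss, and only against the margin.
- **That the within-patient reading biases the difference or raises the false-positive rate.** This needs patients with a baseline value only. Were they 5% of the total and carried forward with zero change, the estimate would be 2.3 × 0.95 = 2.19, and dropout of 25% against 15% would put the one-sided error against zero at about 5–6%. The stated full analysis population excludes them. With them removed, the estimate returns to 2.3 and the error to about 2.2–2.8%.
- **That carrying the last value forward is a routine second step.** It applies only where no trend can be computed. With at least two values per patient, a within-patient line can nearly always be fitted. It matters mainly if the intention-to-treat set means all randomised patients, which the article does not settle.

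The defence does not show a reason to impute. The wording leaves both readings open, and on neither does the rule improve materially on the model already planned.

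**Conclusion.** The point holds in limited form and should be fixed. The article fixes a deterministic single imputation that is ambiguous and, under missing at random, unnecessary for the planned mixed model. Across patients, it shrinks 2.3 to about 1.84, with coverage near 75% and power of 58–66%, or about 30–41% if loss follows progression. Within patient, the cost is variance rather than bias: power of roughly 73–93% with dropout spread over visits, against 91–95% for the mixed model.

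These sizes rest on the article's difference, SD, margin and 20% loss, and on assumed visit noise (SD 1 to 2.5), linear decline, baseline distribution and dropout timing. The imputed results are for a two-group comparison of 12-month change. They also take the margin of 1 as the tested null, which is inferred from the sample size; against zero the loss of power is small. The article does not establish which reading is meant, so the larger figures are a risk and not a forecast.

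**What to change.** 1. Delete the linear-trend and carry-forward rule for the primary eGFR analysis.
2. State that the primary analysis is the repeated-measures mixed model, fitted by REML to all observed eGFR values with no imputation.
3. State whether the intention-to-treat set is the full analysis population or all randomised patients.
4. Add one sensitivity analysis for data not missing at random, because withdrawal for permanent renal replacement or death may break that assumption. Examples are multiple imputation by arm with a delta shift, or a joint model of eGFR with renal replacement and death.

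The cost is wording and some programming, with no new data. The primary analysis will then rely openly on missing at random, which is why the sensitivity analysis belongs with it. The change must be in place before unblinding; the planned confirmation of the analysis plan at blind data review gives the opportunity.
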